## Abstract

**Background:**

Rheumatoid Arthritis (RA) commonly affects the hands and wrists with inflammation, deformity, pain, weakness and restricted mobility leading to reduced function. The effectiveness of exercise for RA hands is uncertain, although evidence from small scale studies is promising. The Strengthening And Stretching for Rheumatoid Arthritis of the Hand (SARAH) trial is a pragmatic, multi-centre randomised controlled trial evaluating the clinical and cost effectiveness of adding an optimised exercise programme for hands and upper limbs to best practice usual care for patients with RA.

**Methods/design:**

480 participants with problematic RA hands will be recruited through 17 NHS trusts. Treatments will be provided by physiotherapists and occupational therapists. Participants will be individually randomised to receive either best practice usual care (joint protection advice, general exercise advice, functional splinting and assistive devices) or best practice usual care supplemented with an individualised exercise programme of strengthening and stretching exercises. The study assessors will be blinded to treatment allocation and will follow participants up at four and 12 months. The primary outcome measure is the Hand function subscale of the Michigan Hand Outcome Questionnaire, and secondary outcomes include hand and wrist impairment measures, quality of life, and resource use. Economic and qualitative studies will also be carried out in parallel.

**Discussion:**

This paper describes the design and development of a trial protocol of a complex intervention study based in therapy out-patient departments. The findings will provide evidence to support or refute the use of an optimised exercise programme for RA of the hand in addition to best practice usual care.

**Trial registration:**

Current Controlled Trials ISRCTN89936343

## Background

Rheumatoid arthritis (RA) is the most common inflammatory polyarthritis
[1]. It is a chronic unpredictable disorder that can cause persistent joint pain, joint damage and long-term disability (especially in the hands and feet). The prevalence of RA is 1.16% in women and 0.44% in men, increasing with age to 5% in those aged over 55
[1]. Five years after diagnosis, 40% of people with RA have relatively normal function (13% in remission), 44% have mild to moderate disability, and 16% have marked functional disability
[2]. Particular problems for the hands and wrists are inflammation, deformity, pain, weakness and restricted mobility resulting in loss of function
[3].

Although there is no cure for the disease, there are increasingly effective drug treatments that can reduce the impact of the disease, notably disease-modifying anti-rheumatic drugs (DMARDs). The overall goals of management are to prevent or control joint damage, maximise function and decrease pain
[4]. All current UK clinical guidelines for the management of RA recommend the use of physiotherapy (PT) and occupational therapy (OT) as an adjunct to drug treatment
[5,6]. The three most common components of PT/OT for RA hands are exercise therapy, joint protection advice and provision of functional splinting and assistive devices
[7].

A systematic review
[8] of six randomized controlled trials (RCTs) of the effectiveness of exercise programmes in RA for the whole body concluded that dynamic exercise (aerobic capacity and/or muscle strength training) was effective in improving muscular endurance and strength, without detrimental effects on disease activity or pain. The number of RCTs that have specifically investigated the effects of exercise on RA hands is limited to five small studies (n=55,100, 67, 52 and 57 patients respectively) with mostly short term follow up of a few months
[9-13]. Each of these studies demonstrated small improvements in hand strength or function using exercise, with no increase in joint swelling, pain or disease activity. The long term effectiveness of exercise for RA hands has not been established.

The economic cost of RA is thought to be substantial for both the individual patient and society as a whole
[4,14]. The highest costs are associated with those patients that have poor and declining function early on in their disease
[15].

### Aims

This paper describes the trial protocol of a large pragmatic randomised controlled trial to evaluate the clinical and cost effectiveness of adding an optimised exercise programme for hands and upper limbs to best practice usual care for patients with RA. An additional aim is to describe, qualitatively, the experience of participants with a particular emphasis on patient expectation, exercise behaviours, and reasons for adherence/non-adherence.

## Methods

### Trial design

The SARAH trial is a pragmatic, multi-centre randomised controlled trial (Figure 
1).

**Figure 1 F1:**
[figure not shown]
Flowchart of study design.

### Participants

480 participants will be recruited from direct referrals from Rheumatology clinics and from those referred to PT/OT clinics. 17 NHS trusts in England will recruit participants.

In addition to the recruitment of newly referred patients, a number of the Rheumatology and some of the PT/OT participating departments have a review register of ‘chronic’ patients, periodically called in for review appointments. Provided that these patients meet the selection criteria described below, they will be approached to participate in the trial.

### Selection criteria

All patients with Rheumatoid Arthritis meeting the American College of Rheumatology clinical and immunological criteria
[4], with pain and dysfunction of the hands and/or wrist joints who are either not on a disease modifying medication (DMARD), or who have been on a stable DMARD regimen for three months or more, will be included in the trial. Those fulfilling any of the following criteria will be excluded:

i. Aged less than 18 years.

ii. Patients who have experienced upper limb joint surgery, or fracture, in the previous six months.

iii. Patients on a waiting list for upper limb orthopaedic surgery.

iv. Patients who are pregnant.

Patients will be asked to give written informed consent according to principles of Good Clinical Practice and the Declaration of Helsinki
[16]. At the time of consent, outcome assessors will collect baseline measures.

### Randomisation

Randomisation to the exercise programme or usual care will be via a central telephone randomisation service at Warwick Clinical Trials Unit, University of Warwick. The randomisation schedule will be prepared by the trial statistician (CM). Randomisation will be stratified by centre using a variable block size.

### Allocation concealment

Eligibility checks will be performed, and consent for randomisation taken. The research clinician will then telephone the randomisation service, and only once the patient is registered in the trial, will the random allocation be generated. Hence allocation will be concealed.

### Blinding

The outcome assessor will be blind to the group allocation of the participant and will be independent of intervention delivery. Participants will be requested not to disclose group allocation to the outcome assessor. If an outcome assessor is unblinded, this will be recorded. All assessors will be asked to guess which allocation they think the participant has been given at both follow-up time points. The patients and therapists providing the treatment cannot be blinded to the group allocation.

### Baseline assessment

After participants have been assessed for eligibility and consent has been gained, baseline assessment will be carried out. Questionnaires will be completed whilst the outcome assessor conducts randomisation followed by a physical assessment (both participant and assessor will be unaware of allocation at this appointment). The baseline measures are summarised in Table 
1. A Research Clinic Questionnaire will record demographic details (age, sex, date of RA diagnosis, ethnicity, marital status, hand dominance) and the Michigan Hand outcomes Questionnaire (MHQ)
[17], The MHQ has shown to be a reliable, valid and responsive measure for an RA population
[18-20] and contains six domains (1) overall hand function, (2) Activities of Daily Living (ADL), (3) pain, (4) work performance, (5) aesthetics, and (6) patient satisfaction. Scores range from 0 to 100, with higher scores indicating better performance, except for the pain scale. For the pain scale, a higher score indicates more pain.

**Table 1 T1:** Summary of measures to be collected

**Domain**	**Data source**	**Measures – Instrument (Scale – high value is better score unless specified)**	**Time points**
Function	Research Clinic Questionnaire (participant reported)	Michigan Hand Outcomes Questionnaire (MHQ)– overall Hand function score (0–100)	0, 4, 12
		Michigan Hand Outcomes Questionnaire (MHQ)– overall score (0–100)	
Pain	Research Clinic Questionnaire	Pain sub-scale of MHQ (0–100; high score is worse)	0, 4, 12
		‘Troublesomeness’ rating (0–20; high score is worse)	
Impairment	Research Clinic Examination (performed by outcome assessor)	Joint deformity (MCPJ only) – goniometer (Degrees; high score is worse)	0, 4, 12
		Wrist range of motion (flexion/extension) – goniometer (Degrees)	
		Finger range of motion (combined flexion and combined extension) – Ruler (mm; high score is worse for combined flexion)	
		Thumb opposition range of motion - observation (0–10)	
		Dexterity - timed 9 hole peg test (Seconds; high score is worse)	
		Grip and Pinch Strength – dynamometer (Newtons)	
Disease Activity	Medical Records Research Clinic Examination	Erythrocyte sedimentation rate (ESR – mm/h) and/or C-Reactive protein (CRP – mg/l) blood test	0, 4, 12
		Hand and wrist joint tenderness and swelling count – examination (0–22; high score is worse)	
Health-related Quality of Life	Research Clinic Questionnaire	SF-12(0-100)	0, 4, 12
		EuroQol EQ-5D (health utility)(0–1)	
Self-efficacy	Research Clinic Questionnaire	7 item questionnaire	0, 4, 12
Satisfaction	Research Clinic Questionnaire	Treatment satisfaction item	4,12
		Satisfaction sub-scale of MHQ (0–100)	
Global Change	Research Clinic Questionnaire	Participant-rated global change question(7 point Likert scale)	4, 12
Adherence	Research Clinic Questionnaire	5 item questionnaire	0, 4, 12
Economics	Research Clinic Questionnaire	Resource use questionnaire	4, 12

The questionnaire will also contain measures of pain troublesomeness
[21], self-efficacy
[22], the EuroQol EQ5D
[23], the 12 item short form health survey (SF-12)
[24], health economics-related questions (employment status, sick days in past month due to RA in wrists/hands, benefits, highest educational qualification, household income) and treatment preference. Blood test results (CRP, ESR, serum rheumatoid factor) and current medication (prescribed and as required in last 7 days) will be taken from hospital and prescription records. The outcome assessor will be present to answer any questions regarding the measures but will be trained not to influence the participant’s responses.

Following completion of the case report form, a physical assessment will be performed in a standardised order and standardised positions. This will include the measurement of joint deformity (MCP ulnar/radial deviation in maximum pronation, where ulnar deviation is recorded as a positive value) and active range of motion (wrist flexion and extension from the neutral position with a goniometer
[25], combined finger flexion according to Ellis and Bruton
[26], combined finger extension and thumb opposition according to Kapandji
[27]). A modified swollen and tender joint count (22 joints of hand and wrist
[28]) will be taken, along with a test of upper limb dexterity (Nine-hole peg test according to Mathiowetz et al.
[29]). Finally, two forms of grip strength (full-hand and tripod pinch will be measured using the MIE Digital Grip Analyser
[30]. The standard test position recommended by the American Society of Hand Therapists will be used
[31]. Patients will be sat in a straight-backed chair without arm rests, feet flat on floor, the shoulder of the assessed limb will be relaxed by the side, the elbow flexed to 90 degrees, the wrist will be extended and in ulnar deviation between 0 and 15 degrees and the forearm rotated to neutral pronation/supination. The mean of three maximal three-second grips will be calculated for each hand, with 60 second rests between repetitions.

### Interventions

The rationale and protocol for the interventions are described in a separate paper
[32]. All interventions are delivered by PTs or OTs experienced in the treatment of hand and rheumatology conditions. The therapists will be independent of the recruitment and randomisation procedures and will attend a training session by the trial team and receive a training and reference manual as well as on-going support and guidance regarding the intervention to ensure quality standards are met. Therapists will be permitted to deliver both the experimental and control interventions, and each treatment session will be recorded in a treatment log. Contamination will be minimized through monitoring of treatment logs completed at each session, quality assurance visits to each therapist at the beginning of their time delivering interventions on the trial and also limitation of additional therapy materials (Patient exercise booklets, therapeutic putty, Thera-band® resistive band and hand exercisers) sufficient to only cover participants randomised to the experimental arm of the study. The aim is for all treatments to be completed within four months of the baseline assessment. Figure 
2 provides an overview of the interventions.

a. Control intervention – Best Practice Usual Care only

**Figure 2 F2:**
[figure not shown]
Flowchart of interventions.

Participants randomised to the control intervention will have between one and three sessions of outpatient therapy with a maximum total contact time of one and a half hours. Treatment will include the provision of joint protection information, splinting, assistive devices and other general advice as required. The number of sessions will depend on quantity of advice and education required and/or for review of splinting/assistive devices. This will be determined by the stage and severity of the disease. The choice of treatments was made using two principles; first, there is evidence that the treatments are effective for hand dysfunction in RA
[33], and second, the treatments are consistent with current clinical guidelines
[5,6]. Both control and experimental interventions were developed using focus group meetings with stake holder clinicians from across the UK.

b. Experimental intervention – Best Practice Usual Care supplemented with an optimised exercise programme

Participants randomised to the exercise programme will receive the usual care package plus an additional five sessions with a therapist over a 12 week period. The aim will be to increase hand function using exercises to stretch and strengthen the muscles and tendons, as well as mobilise the joints of the hand and wrist and improve dexterity. This will be supported by a Home Exercise Programme (reinforced by a behavioural activation approach and exercise diary) to be performed daily. This number of contacts, spread over this period, allows maximum progression of the intensity of exercise and sufficient time for a physiological response in the neuromuscular system to significantly improve function
[34]. The intervention will use a standardised protocol of progression and, if necessary, regression of exercise intensity. A modified Borg scale of perceived exertion
[35] will be used to regulate the intensity of resistance exercise. The programme is based on the existing evidence base, a professional consensus of UK PT/OTs and a programme that has some evidence of short-term effectiveness
[36]. Adherence with the exercise programme is vital to ensure the dosage required to strengthen muscle and improve mobility is achieved. Evidence based strategies to maximise adherence will be incorporated into each treatment session, including effective goal setting and action planning
[37,38].

Treatment fidelity will be evaluated by recording content of sessions on treatment logs and the number of sessions attended by participants in both arms of the trial. Quality assurance checks will be made by the clinical research fellow who will observe treatment sessions for all therapists. We will also evaluate whether participants have progressed exercises within the exercise arm using information from the treatment logs and exercise diaries.

### Other treatments

Participants may seek other forms of treatment during the follow-up period. Additional treatments, including contacts with their GP or other health professional, changes in types of medication, use of physical treatments or alternative therapies, will be recorded as a treatment outcome.

### Follow-up data collection

Follow-up data collection will be by face-to-face clinical assessment at four and 12 months. Where face-to-face clinic assessment is not possible, postal and telephone data collection methods will be used to obtain core data. The outcome measures have been described in the baseline assessment section and are detailed in Table 
1. The primary outcome measure will be the 12 month Michigan Hand Outcome Questionnaire (MHQ) overall hand function subscale score.

### Sample size

A standardised mean effect size of 0.3 is reported to represent a clinically important difference in hand function in this group
[39]. A previous small study using a similar intervention found a mean benefit of 0.7 in the AIMS2 with a standard deviation of 1.81 and a standardised effect size of 0.39
[36]. This suggests that in this larger, more pragmatic multi-centre trial, a standardised effect size of 0.3 in a similar function score of the MHQ is realistic and meaningful. To show this difference with 80% power at the 5% significance level, we require data on at least 352 participants (using SAS procedure GLMPOWER). Assuming a worst case scenario of 25% loss to follow-up, this would require 470 participants to be recruited initially.

Over 15 months we expect 1,200 people with hand RA to be referred to our participating centres. If half of these are assessed for study entry and 80% of these join the study, we will have 480 participants (1,200*0.5*0.8). This is our target sample size (Figure 
1). The assumptions underlying the sample size calculation will be monitored by the Data Monitoring Committee.

### Statistical analysis

Patients will be analysed in the treatment group to which they were randomised, regardless of the treatment that they actually received
[40]. The trial will be reported to CONSORT guidance and standards
[41], and all estimates will be reported 95% confidence intervals. Demographic, clinical characteristics and baseline measurements will be presented to compare the trial groups and generalisability to clinical settings.

#### Primary outcome

The difference between the intervention and best practice usual care groups in mean MHQ overall hand function subscale score at 12 months will be analysed by a linear model, adjusted for the baseline score. Adjustment will be made for centre, sex and age. Further adjustment by disease activity, medication and other patient characteristics will be considered if there are imbalances between the intervention groups.

#### Secondary outcomes

Differences between groups for MHQ overall hand function score at 4 months, overall MHQ score at 4 and 12 months, measures of pain (sub-scale of MHQ and ‘troublesomeness’), impairment measures, self-efficacy, joint counts, and quality of life (SF-12 and EQ-5D) scores will be analysed in a similar manner to the primary outcome measure.

Analyses will also take account of baseline drug regimens (no DMARD, single DMARD, combination DMARD or biologic DMARD) and disease duration (< or > 5 years since diagnosis). The impact of therapist effects will be explored by including a random therapist effect nested within centre in the various models. The effect of missing data will be investigated using multiple imputation analysis.

Complier-average causal effect (CACE) will be estimated using an instrumental variable method
[42]. Statistical analyses will be performed using SAS V9.2 software.

### Economic evaluation

The economic analysis will include a ‘within-trial’ cost-utility analysis, and modelling to estimate longer-term costs and health effects if justified by the clinical results.

For the within-trial analysis, costs incurred and Quality-Adjusted Life Years (QALYs) attained over the twelve month study period will be estimated at the individual patient level. The EuroQol (EQ-5D) will be used to generate individuals’ utility scores at 0, 4 and 12 months (using the UK Social Tariff
[43]), and QALYs will then be calculated over this period using an area-under-the-curve approach. Similarly, self-reported resource use data collected at 4 and 12 months will be used to estimate individuals’ hand RA related health and social care costs over the 12 month study period. The cost of the exercise intervention will be estimated from PT and OT records of time spent with patients, and of any consumables used. Costs will be estimated from an NHS and Personal Social Service perspective (as recommended by NICE
[44]), as well as from a broader societal perspective (including patient expenditure). Unit costs for publicly funded services will be taken from standard national sources
[45], costs of private services will be obtained directly from patients. As for clinical outcomes, missing resource use and QALY data will be estimated by multiple imputation.

A regression approach will then be used to estimate between-group differences in mean costs and QALYs, adjusting for centre, sex, age and other baseline differences between the study groups. An Incremental Cost-Effectiveness Ratio (ICER), the additional cost per additional QALY gained with the exercise programme compared with best usual practice alone, will be calculated if appropriate. Interaction terms will also be used to investigate possible treatment moderators and hence to identify patient subgroups for whom treatment cost-effectiveness is predictably different: age, sex, disease activity, medication group, duration of disease, or other relevant patient characteristics.

The twelve-month time horizon of the within-trial analysis is quite limited. It is possible that extrapolation of costs and QALYs beyond this time might lead to different conclusions about cost-effectiveness. For example, if participants randomised to the exercise programme had greater quality of life at twelve months than those randomised to usual care alone, but that this health gain came at a relatively high cost, then it is possible that further accumulation of quality of life gains and/or cost savings after the first year could bring the ICER below the £20,000 to £30,000 per QALY gained threshold that is usually considered to be cost-effective in the UK
[46]. If so, we will use decision-analytic modelling with probabilistic sensitivity analysis to extrapolate expected costs and health effects.

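### Resource use is not asked at baseline, so the cost regression has no prior health and social care cost to adjust for; the loss is one of precision, not bias

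*Protocol article*

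**What the plan says.** The Economic evaluation section sets a 12-month horizon: "costs incurred and Quality-Adjusted Life Years (QALYs) attained over the twelve month study period will be estimated at the individual patient level". For costs, "self-reported resource use data collected at 4 and 12 months will be used to estimate" each participant's hand-related health and social care costs. The Economics row of Table 1 agrees: "Resource use questionnaire 4, 12". The cost of the exercise programme is taken separately, from therapists' records of contact time and consumables.

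QALYs are treated differently, with "utility scores at 0, 4 and 12 months".

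The Baseline assessment section lists several economic items at entry: employment status, "sick days in past month due to RA in wrists/hands", benefits, education and household income. It adds that "current medication (prescribed and as required in last 7 days) will be taken from hospital and prescription records". No contacts with health or social care services are listed at baseline.

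Mean cost and QALY differences are to be estimated by regression, with centre, sex, age and further baseline differences between the arms as covariates. Baseline cost is not named. Missing resource use is to be multiply imputed.

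**The concern.** In a chronic disease, past service use tends to predict later service use. This trial recruits both newly referred patients and patients on review registers (Participants section), so prior use is likely to vary widely. Randomisation is stratified by centre only. If one arm happens to receive more heavy users, that imbalance enters the incremental cost, and so the ICER, with no direct measure by which to adjust for it.

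Cost stands apart from the other modelled outcomes here. The primary outcome is adjusted for its own baseline score, the secondary clinical outcomes follow the same pattern, and EQ-5D has a month-0 value.

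The point belongs to the protocol and cannot be left to a later analysis plan, because no analysis can recover a baseline questionnaire that was never given.

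**Working it through.** **Step 1: which outcomes have a baseline value.**

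| Modelled outcome | Collected at (months) | Own baseline available? |
|---|---|---|
| MHQ hand function (primary) | 0, 4, 12 | Yes, in the model |
| Pain, impairment, joint counts, self-efficacy, SF-12 | 0, 4, 12 | Yes |
| EQ-5D, for QALYs | 0, 4, 12 | Yes |
| Self-reported resource use, for costs | 4, 12 | No |

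Table 1 and the Economic evaluation text agree on the last row, so it is not a slip in one place.

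**Step 2: what baseline cost would add.** The article gives no figure for the economic analysis to reproduce, and no correlation between prior and trial-period cost. That correlation, r, is an assumption: 0.3 to 0.5 as the working range, 0.2 to 0.6 as a wider one. In a randomised comparison, adjusting for one baseline covariate multiplies the variance of the difference by 1 − r² and the standard error (SE) by √(1 − r²).

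| r | 1 − r² | √(1 − r²) | Reduction in SE |
|---|---|---|---|
| 0.2 | 0.96 | 0.980 | 2% |
| 0.3 | 0.91 | 0.954 | 5% |
| 0.4 | 0.84 | 0.917 | 8% |
| 0.5 | 0.75 | 0.866 | 13% |
| 0.6 | 0.64 | 0.800 | 20% |

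**Step 3: the same gain in participants.** The Sample size section requires 352 participants with data. That figure reproduces: a standardised effect of 0.3, two-sided 5% and 80% power in a two-sample t-test give 175.4, so 176 per arm and 2 × 176 = 352. It was set for hand function and serves here only as a scale. At r = 0.3, 352 / 0.91 = 387, equivalent to 35 more participants. At r = 0.5, 352 / 0.75 = 469, equivalent to 117 more.

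**Step 4: why these are upper values.** The r above is the plain correlation. What counts is the information that baseline cost adds to the covariates already in the model or open to it: centre, sex, age and other recorded characteristics such as medication and disease activity. Some of what prior cost would explain is already explained by these, so the real gain is smaller.

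**Step 5: the follow-up interval.** Months 4 to 12 are (12 − 4) / 12 = 67% of the study period and appear to rest on the second self-report. This is a share of time, not of cost. The article does not state how far back either questionnaire asks.

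**The case against.** The best defence is that nothing here is wrong or contradictory. Text and table agree, and the plan never promises to adjust for baseline cost. Valid inference on the cost difference does not need that covariate. This stands, and it limits the point to a cheap improvement.

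Four stronger readings may tempt a reader, and the document does not support them.

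- **That baseline holds nothing relevant to cost.** It records medication, which is itself a health care resource, as well as sick days, benefits and employment. The open-ended adjustment for further baseline differences allows their use. They remain partial proxies: none counts visits, admissions or social care.
- **That the ICER is biased.** Randomisation prevents a systematic difference in prior use. What is lost is precision and the correction of chance imbalance.
- **That an eight-month recall loses a calculable part of the costs.** Eight months is an inference from the spacing of the two questionnaires. A shorter window with extrapolation would also fit, and an article commonly leaves such wording to the full protocol. Any miss rate would be a guess, and under-reporting of the overall level does not by itself show an effect on the ICER.
- **That two thirds of the cost rests on one self-report.** Programme cost comes from therapist records, and treatment is meant to finish within four months. The Other treatments section also says that further contacts and medication changes will be recorded, without saying by what method.

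**Conclusion.** The point holds as a minor design limitation confined to the economic evaluation. No health and social care cost is collected for the period before randomisation, so the cost regression cannot adjust for it, and the recorded items replace it only in part. The consequence is a wider interval for the incremental cost than necessary and no direct correction of a chance imbalance in prior use. It is not a systematic bias.

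Under an assumed correlation of 0.3 to 0.5, the forgone reduction in SE is at most about 5% to 13%, and less given the existing covariates. The size depends entirely on that assumption; the absence of the covariate does not. No conclusion is drawn about recall error. The primary outcome, its analysis and the sample size are untouched.

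**What to change.** Give the resource use questionnaire at the existing baseline visit as well, with the same content as at follow-up and a stated period before consent. Add month 0 to the Economics row of Table 1. According to the Baseline assessment section, participant and assessor do not know the allocation at that appointment, so the answers could not be influenced by it.

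In the Economic evaluation section, name the resulting baseline cost as a covariate in the cost regression and include it in the multiple imputation model for missing resource use. The imputation use matters because the Sample size section allows for up to 25% loss to follow-up.

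The cost is a few minutes of each participant's time and some data entry, with no new visit. An extract of hospital contacts is not proposed: the article shows record access for blood results and medication only, and such an extract would mean extra work at sites.

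### Adjustment of the QALY difference for baseline EQ-5D utility is left to an open phrase that reads as depending on observed imbalance; it should be fixed in advance

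*Protocol article*

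**What the plan says.** The Economic evaluation section of the protocol article states that the EQ-5D "will be used to generate individuals’ utility scores at 0, 4 and 12 months", and that "QALYs will then be calculated over this period using an area-under-the-curve approach". Month-0 utility is therefore part of the outcome. The same section then says that regression will be used to compare the groups on "mean costs and QALYs, adjusting for centre, sex, age and other baseline differences between the study groups". Three covariates are named. Anything further, baseline utility included, falls under the closing words.

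Two other sections are more definite. Under Primary outcome, the 12-month hand function score "will be analysed by a linear model, adjusted for the baseline score". Centre, sex and age are added, and only further characteristics are made to depend on imbalance. Under Secondary outcomes, "quality of life (SF-12 and EQ-5D) scores will be analysed in a similar manner to the primary outcome measure". That covers EQ-5D scores but does not mention QALYs.

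**The concern.** A QALY computed as an area under the curve contains the baseline utility, and baseline utility usually predicts follow-up utility. Its case for adjustment is therefore at least as strong as that of the baseline hand function score in the primary model. The article gives the primary outcome a firm commitment and gives the QALY only an open phrase worded around differences between the groups.

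Observed imbalance is a poor trigger here for two reasons. First, a baseline difference of one standard error or more, in either direction, arises by chance in about 32% of trials and would not usually be remarked on, yet it moves the QALY estimate. Second, the gain in precision from adjustment is available even when the groups are perfectly balanced, and an imbalance rule would forgo it.

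The QALY difference is the denominator of any ICER, which the article compares with £20,000 to £30,000 per QALY. The trial could also report a baseline-adjusted EQ-5D effect beside a QALY effect, from the same data, that is not adjusted, with no reason given.

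**Working it through.** **The plan's own figures.** The article gives no figure for the QALY analysis. Its sample size supplies the numbers of participants used below and reproduces: a two-sample t-test with effect size 0.3, 80% power and two-sided 5% significance needs 175.4 per arm, so 176 per arm and 352 in total; 352 / 0.75 = 469.3, so 470. The recruitment target is 480.

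**Inputs.**
- From the article: utilities at 0, 4 and 12 months; 352 participants with data as the minimum, 480 as the target.
- Assumed, because the article does not give them: utility SD of 0.20 to 0.30, equal at all times; a common correlation r of 0.3 to 0.7 between any two times; equal arms; straight lines between measurement points.

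**Step 1, weights in the QALY (in years).** Month 0: (4/12)/2 = 1/6. Month 4: (4/12)/2 + (8/12)/2 = 1/2. Month 12: (8/12)/2 = 1/3. They sum to 1.

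**Step 2, carry-over per unit of baseline difference, without adjustment.** 1/6 + r × (1/2 + 1/3) = 1/6 + 5r/6. This gives 0.17 at r = 0 (the direct share alone), 0.42 at r = 0.3, 0.58 at r = 0.5 and 0.75 at r = 0.7.

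**Step 3, a one-standard-error baseline imbalance.** SE = SD × √(4/N). Multiplying by the carry-over gives the shift in the QALY difference:

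| N | SD | SE of baseline difference | r = 0.3 | r = 0.5 | r = 0.7 |
|---|---|---|---|---|---|
| 480 | 0.20 | 0.0183 | 0.0076 | 0.0107 | 0.0137 |
| 480 | 0.25 | 0.0228 | 0.0095 | 0.0133 | 0.0171 |
| 480 | 0.30 | 0.0274 | 0.0114 | 0.0160 | 0.0205 |
| 352 | 0.20 | 0.0213 | 0.0089 | 0.0124 | 0.0160 |
| 352 | 0.25 | 0.0267 | 0.0111 | 0.0155 | 0.0200 |
| 352 | 0.30 | 0.0320 | 0.0133 | 0.0187 | 0.0240 |

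The range is 0.008 to 0.024 QALYs. In money that is about £150 to £480 per participant at £20,000 per QALY, and about £230 to £720 at £30,000.

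**Step 4, precision.** In units of SD², the QALY variance is (1/36 + 1/4 + 1/9) + 2r × (1/12 + 1/18 + 1/6) = 0.389 + 0.611r. The share explained by baseline utility is (1/6 + 5r/6)² divided by that variance, and the ratio of standard errors is √(1 − share).
- r = 0.5: share 0.340/0.694 = 0.49; ratio √0.51 = 0.71.
- r = 0.7: share 0.5625/0.817 = 0.69; ratio √0.31 = 0.56.

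With N = 480 and SD 0.25, the standard error of the QALY difference falls from 0.0190 to 0.0136 (r = 0.5) or from 0.0206 to 0.0115 (r = 0.7). These ratios compare a model containing baseline utility alone with a model containing no covariates.

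**Step 5, check by simulation.** In 3,000 simulated trials with no treatment effect (N = 480, SD 0.25, r = 0.5), the slope of the estimated QALY difference on the baseline difference was 0.59 unadjusted and 0.01 adjusted. The standard deviation of the estimate was 0.0193 unadjusted and 0.0137 adjusted. Both estimators averaged zero to within 0.0002.

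**The case against.** The strongest reply is that this is a condensed article. The full covariate list of an economic regression is something an article may leave to the analysis plan, and that plan is not shown. Nothing in the article excludes baseline utility, and the open words can be read to include it. They contain no explicit condition, whereas the Primary outcome section does write one for its further covariates. The commitment for EQ-5D scores suggests that the authors favour baseline adjustment.

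Much of this stands, and it limits the point to a matter of commitment. But the article is not silent. It states a covariate rule, and the only route that rule leaves for baseline utility is worded in terms of differences between the groups. The commitment under Secondary outcomes does not extend to QALYs.

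A reader might also infer more than the documents support:
- **That a baseline imbalance passes in full into the QALY gain.** That would require no adjustment for utility at all, which the article does not say. Even then the carry-over is a fraction (Step 2).
- **That the ICER would be biased.** Randomisation makes both estimators unbiased, and the unadjusted interval already reflects the chance variation. What is lost is precision, and protection against the particular imbalance that happens to occur.
- **That a chance imbalance could equal a realistic QALY gain.** The article gives no expected QALY gain, so there is no figure to support the comparison.
- **That the interval would narrow by the ratios in Step 4.** The stated model already contains centre, sex and age. If these explain some of the utility, both the narrowing and the carry-over would be smaller.

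**Conclusion.** The point holds in a limited form. For the QALY difference, adjustment for baseline utility rests on an open phrase that reads as depending on observed imbalance, while the article commits to baseline adjustment for the primary outcome and for EQ-5D scores. If utility were left out, a one-standard-error chance imbalance would shift the QALY difference by roughly 0.008 to 0.024, and the standard error would be larger than it need be. The size rests on an SD and correlations that the documents do not supply, and on a comparison with a model without covariates. The consequence is avoidable chance error and inefficiency in a secondary, economic analysis whose ICER is to be calculated only where appropriate. It does not touch the primary outcome. It is best treated as a free improvement.

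**What to change.** State in the Economic evaluation section, or in the analysis plan if it does not already say so, that the QALY regression will include baseline EQ-5D utility, together with centre, sex and age, for all participants and regardless of any observed imbalance. Leave the cost model and any other prespecified covariates as they are; nothing here argues for changing them.

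The cost is one sentence and one extra coefficient in the model. The EQ-5D is already scheduled at month 0 in Table 1, so no new data collection is needed.
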